### Study Design

This pilot study is a 12-week unblinded randomized controlled trial with two intervention groups (group 1: teletherapy/live online; group 2: video on demand) in comparison to a control group (group 3: watch and wait). The study is designed to evaluate feasibility and acceptability, as well as to obtain preliminary evidence on efficacy. The observational period comprises 24 weeks: a baseline assessment (T0) and a 12-week intervention phase with subsequent online questionnaire and testing (T1). At week 24 (T2), study participants will be asked to fill out questionnaires and participate in interviews, and a second round of online testing will be conducted. Given the digital nature of ErgoLoCo, the entire study process, including enrollment, treatment, interviews, and testing, will be performed through online visits.

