**Mixed methods study on acceptability and feasibility (primary outcome)**			
	Acceptance and feasibility of the online program	Semistructured interviews with 12 participants of each treatment group	Week 6 and week 12
	Acceptance and feasibility of the online program	Questionnaire assessing 35 Likert-scaled items developed based on the theoretical framework of acceptability in all participants [26]	Week 24
	Acceptance and feasibility of the online program	Focus group meeting notes on acceptance and feasibility of the online program by occupational therapists providing live-online sessions	Week 12

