#### Statistical Analysis Plan

All quantitative data will be prepared using Microsoft Excel or SPSS software and analyzed with R statistical packages. Data visualizations will be created using GraphPad Prism and R software tools. Analysis of the following items is planned from the time points 0 weeks (T0), 12 weeks (T1), and 24 weeks (T2): impairments in daily life activities, family and social life, stress, and sexual activity, and deficits in concentration, attention, and mental speed, particularly focusing on visual attention, physical, mental, and social symptoms of PCS, including concentration, attention, mental speed, mobility, self-care, usual activities, pain, disabilities, anxiety, and depression. An intention-to-treat approach will be used. Estimates and 95% CIs will be computed for the mean, median, and selected lower quantiles. To compare time points, *t*, Wilcoxon-Mann-Whitney, and Kolmogorov-Smirnov tests will be applied, including corrections for multiple testing. Scores derived from questionnaires will be analyzed concerning change over time using *t* and Wilcoxon-Mann-Whitney tests, including corrections for multiple testing. Effect sizes will also be computed. Furthermore, at T0, T1, and T2, we will assess whether certain factors such as age or education influence the feasibility of therapy experiences using *t*, Wilcoxon-Mann-Whitney, and Fisher exact tests as appropriate.

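### The analysis of whether age or education influences therapy experiences is planned at T0, before any therapy, and its two-group tests suit the Likert scores poorly

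*Protocol article*

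**What the plan says.** The last sentence of the Statistical Analysis Plan section commits to this: "at T0, T1, and T2, we will assess whether certain factors such as age or education influence the feasibility of therapy experiences". The tests are t, "Wilcoxon-Mann-Whitney, and Fisher exact tests as appropriate". The same section sets T0, T1 and T2 at 0, 12 and 24 weeks, and Study Design describes the sequence as "a baseline assessment (T0) and a 12-week intervention phase", so T0 precedes therapy.

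The feasibility and acceptability measures are in Table 1 and in Outcomes (Primary Study End Points):

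- "Semistructured interviews with 12 participants of each treatment group", at weeks 6 and 12.
- "Questionnaire assessing 35 Likert-scaled items developed based on the theoretical framework of acceptability in all participants", at week 24.
- A focus group with the therapists, at week 12.
- A short online questionnaire (four Likert items, two open questions) after each of the six modules, for both intervention groups (n=80).
- Participation rates in the follow-up examinations.

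Table 1 lists age and education level as recorded at enrollment only. Under Intervention Delivery, the watch-and-wait group receives the video materials only after study completion.

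**The concern.** An analysis of what influences therapy experiences needs an outcome, and at T0 there is none. This is a conflict between the analysis text and the schedule, not a detail left to a fuller plan. Feasibility is the primary objective, and this sentence is the one place in the section that explicitly ties named tests to it. An analyst following it literally would have to leave out one time point, or put some other baseline variable in its place and call that feasibility.

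The choice of tests is a second, smaller matter. Age is continuous and the main participant-level experience measures are Likert-scaled. The t and Wilcoxon-Mann-Whitney tests need a two-level grouping variable, and Fisher's exact test needs both variables categorical. No correlation or regression method is named. For age against a score, something must therefore be grouped. Grouping discards information, and a cut point not fixed in advance can be chosen after seeing the data.

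**Working it through.** **1. Is there an outcome at each time point?** There is no stated figure to reproduce, so the check sets the schedule of each measure against T0, T1 and T2.

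Module timing: 24 sessions / 6 modules = 4 sessions per module; at 2 sessions per week this is 4 / 2 = 2 weeks per module. Module questionnaires therefore fall at about weeks 2, 4, 6, 8, 10 and 12. The two-weekly emails with four video links in the video group fit this.

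| Time point | Participant-level measures available |
|---|---|
| T0, week 0 | None |
| T1, week 12 | Module questionnaires, follow-up participation (plus interviews in a subsample) |
| T2, week 24 | Acceptability questionnaire, follow-up participation |

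The earliest measure comes at about week 2. Reading T0 as the time when the factors are recorded does not rescue the sentence: age and education are not recorded again, so T1 and T2 would then have no meaning.

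**2. Which pairings do the named tests accept?**

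| Factor | Feasibility measure | Named test that applies without grouping |
|---|---|---|
| Age | Attended follow-up, yes/no | t or Wilcoxon-Mann-Whitney, comparing age between the two groups |
| Education (categories) | Attended follow-up, yes/no | Fisher exact |
| Education (two levels) | Likert score | t or Wilcoxon-Mann-Whitney |
| Age | Likert score | None; age or the score must be grouped |

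**3. What would grouping cost in the last row?** This is an illustration. The 80 treated participants (40 + 40) come from the protocol. The correlation r, the two-sided alpha of 0.05, normality and the median split are assumptions; the protocol gives none of them.

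- Information kept by a median split of a normal covariate: 2/π = 0.637, about 64%.
- Correlation after the split: r × √(2/π) = 0.30 × 0.798 = 0.239.
- Power by Fisher's z: Φ(atanh(r) × √(n − 3) − 1.96), with √77 = 8.775.
- Age continuous: atanh(0.30) × 8.775 = 0.3095 × 8.775 = 2.716; Φ(0.756) = 0.775.
- Age split: atanh(0.239) × 8.775 = 0.2441 × 8.775 = 2.142; Φ(0.182) = 0.572.

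A simulation of 10,000 trials with the same inputs gave 0.777 and 0.572. Leaving age whole and cutting the score at its lowest fifth instead gave 0.470, so grouping the score has a cost too.

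The same formula over a range of r:

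| Assumed r | Power, age continuous | Power, age median-split |
|---|---|---|
| 0.20 | 43% | 29% |
| 0.30 | 78% | 57% |
| 0.40 | 96% | 83% |

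**The case against.** The strongest reply is that naming T0 is a slip of wording: an analysis without data is simply not run, so no result is biased. The pilot declares its efficacy analyses exploratory, its sample is pragmatic, and it makes no claim of power. The tests are to be used as appropriate, and exact variables and cut points may sit in a fuller plan that is not shown. Most of this stands and is why the point is minor. It does not remove the T0 conflict, which is in the text itself.

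Several stronger readings are tempting, and the document does not support them:

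- *The named tests force age to be split.* They do not. Unsplit age can be compared between those who did and did not attend follow-up, and education is categorical anyway. The plan mentions no dichotomisation.
- *The power figures measure a loss in this trial.* They do not. They describe a split that the plan does not state, at an assumed correlation.
- *T1 has little to analyse.* The acceptability questionnaire is at week 24 only, but the last module questionnaire falls at about week 12, and participation at the T1 examination is known.
- *Age, education and delivery arm are all confounded.* Arm is allocated by urn randomization, so any imbalance in age or education between arms is due to chance. Age and education may well be associated with each other, but the plan claims no adjusted effect.
- *This is the only quantitative analysis of the primary end point beyond description.* The section also plans tests of change over time in questionnaire scores and does not exclude the module questionnaires.

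**Conclusion.** The concern holds in a limited form. One of the three time points (T0) has no feasibility or acceptability measure and cannot be analysed as written; this follows from the schedule alone and needs no assumption. For age against the Likert-scaled scores, the named tests work only after grouping one of the two. That is a weaker method than a simple alternative that uses the same data. Its cost can only be illustrated: about 64% of the information kept under a median split, and power of 57% against 78% at an assumed correlation of 0.30. For binary measures such as follow-up participation the named tests are adequate. Severity is minor: the analysis is exploratory and nothing in the trial's conduct depends on it.

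**What to change.** 1. Delete T0 from this sentence.
2. Restrict the analysis to the two treated arms. Table 1 gives the acceptability questionnaire to all participants, but the control group has had no therapy by week 24.
3. Name the measures: module questionnaires and follow-up participation at T1; acceptability questionnaire and follow-up participation at T2.
4. For the Likert scores, replace the two-group tests with a regression on continuous age, education and delivery arm together. Report estimates with 95% CIs, labelled exploratory. The named tests can remain for binary measures.

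The cost is a change of wording and slightly more analysis work. No new data are needed: age and education are recorded at enrollment, arm is known from randomization, and the scores and follow-up participation are already in the schedule. Sessions completed out of 24 should not be added as an outcome on the strength of this document, which does not list it as a recorded measure.

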#### Analysis of Qualitative Data

All interviews and the focus group will be audio-recorded, pseudonymized, transcribed verbatim, and analyzed using thematic content analysis following the approach of Kuckartz and Rädiker [42], assisted by the MAXQDA analysis software.

### Data Management

All assessment measures will be completed online. The data collected will be categorized in four data sets: (1) personal data such as name and email address; (2) sociodemographic data (eg, clinical characterization, age, gender, migration background, health status, and symptoms), as well as attitudes toward vaccination and experiences with COVID-19 vaccination; (3) test results (scores in cognitive assessments and occupational performance assessments); and (4) qualitative data such as interview transcripts and written interview documentation. Data from the first 3 categories will be incorporated into two independent databases, which are stored separately for data protection reasons.

### Ethical Considerations

The study is registered at the German Clinical Trial Register (DRKS00029990), an approved primary study registry within the World Health Organization network, and has been reviewed by the institutional review boards of participating sites (eg, Hannover Medical School; DEFEAT Corona No. 9948_BO_K_2021). The study is designed as an interventional online pilot study. Interested participants will obtain information about participation in advance on the internet and will be fully informed personally by a study team member about possible benefits and risks of study participation before inclusion. Written informed consent will be obtained from all study participants (as well as from their legal guardians for those younger than 18 years). Additionally, each participant will receive detailed written information on the study and data management procedures. All participants will be informed that their study participation is entirely voluntary and that they can withdraw participation consent at any time without disclosing reasons. Contact information to reach out to the study team for questions via email, telephone, or online meetings at any point during the study will be provided upon enrollment. All data will be collected in pseudonymized form and designated data safety measures have been developed to ensure the privacy of each participant. Personal data will be separated from all other collected data and stored in encrypted form. Qualitative data will be exclusively processed at the University Medical Center Göttingen, and other project team members cannot access these data. Following the transcription of interview notes, transcripts will be pseudonymized and any information (such as location and names of participants) that could enable retrograde identification will be eliminated (ensuring factual anonymization). Audio raw data/video data will be subsequently destroyed. Transcripts will be stored on digital media with password protection in a lockable file cabinet. If a participant does not consent to the use of factually anonymized data for further research projects, transcripts will be destroyed after 10 years. Study participation can be realized entirely from home without any physical or infection risk.

## Results

In this study, we aim to evaluate the feasibility of digital OT as a treatment for clients with PCS. Exploratory analyses will address possible cognitive and performance improvements, QoL, and social participation. The German Ministry of Education and Research provided funding for this research in March 2022 (FKZ 01EP2103A). Data collection is scheduled to take place from October 2022 to August 2023, followed by data analysis between September 2023 and April 2024. We anticipate publishing the results in the fall of 2024.

## Discussion

The ErgoLoCo study is a randomized controlled interventional pilot study designed to gain insight into new therapy options for people affected by long COVID. The intervention was developed to improve occupational performance in relevant everyday occupations and the self-management of PCS-related challenges. As a pilot study, ErgoLoCo is not powered to show treatment efficacy. However, it will provide the first insights into the acceptance and feasibility of a novel OT intervention. The mixed methods approach will provide detailed information on which parts of the intervention will likely impact the well-being of clients with PCS.

Although the current study focuses on long COVID, other medical conditions with similar symptoms, such as myalgic encephalomyelitis or chronic fatigue syndrome, may also benefit from our approach in the future.

A short description of the ErgoLoCo study design will be included in each publication by the study group and this protocol will be referenced. If changes in the study design are necessary, these will be brought to the attention of the institutional review board and will be amended to the study protocol.

The ErgoLoCo pilot study will contribute to developing treatment strategies in PCS, an emerging disease with increasing prevalence, strong socioeconomic impact, and high clinical need.

## Abbreviations

CONSORT: Consolidated Statement of Reporting Trials
COPM: Canadian Occupational Performance Measure
ErgoLoCo: Occupational Therapy (Ergotherapie) for Long COVID
OT: occupational therapy
PCS: post–COVID-19 syndrome
QoL: quality of life
TFA: theoretical framework of acceptability
